## Abstract

**Background:**

Executive function, including prospective memory, initiating, planning, and sequencing everyday activities, is frequently affected by acquired brain injury (ABI). Executive dysfunction necessitates the use of compensatory cognitive strategies and, in more severe cases, human support over time. To compensate for the executive dysfunction experienced, growing options for electronic mainstream and assistive technologies may be used by people with ABI and their supporters.

**Objective:**

We outline the study protocol for a series of single-case experimental designs (SCEDs) to evaluate the effectiveness of smart home, mobile, and/or wearable technologies in reducing executive function difficulties following ABI.

**Methods:**

Up to 10 adults with ABI who experience executive dysfunction and have sufficient cognitive capacity to provide informed consent will be recruited across Victoria and New South Wales, Australia. Other key inclusion criteria are that they have substantial support needs for everyday living and reside in community dwellings. On the basis of the participant’s identified goal(s) and target behavior(s), a specific electronic assistive technology will be selected for application. Both identification of the target behavior(s) and selection of the assistive technology will be determined via consultation with each participant (and their key support person, if applicable). The choice of SCED will be individualized for each participant based on the type of technology used in the intervention, the difficulty level of the behavior targeted for change, and the anticipated rate of change. For each SCED, repeated measurements of the target behavior(s) during the baseline condition will provide performance data for comparison with the performance data collected during the intervention condition (with technology introduced). Secondary outcome measures will evaluate the impact of the intervention. The protocol includes 2 customizable Microsoft Excel spreadsheets for electronic record keeping.

**Results:**

Recruitment period is June 2022 through March 2024. Trial results for the individual participants will be graphed and analyzed separately using structured visual analysis supplemented with statistical analysis. Analysis will focus on important features of the data, including both within- and between-phase comparisons for response level, trend, variability, immediacy, consistency, and overlap. An exploratory economic evaluation will determine the impact on formal and informal support usage, together with quality of life, following the implementation of the new technological intervention.

**Conclusions:**

The study has been designed to test the cause-effect functional relationships between the intervention—in this case, electronic assistive technology—and its effect in changing the target behavior(s). The evaluation evidence gained will offer new insights into the application of various electronic assistive technologies for people who experience executive dysfunction following ABI. Furthermore, the results will help increase the capacity of key stakeholders to harness the potential of technology to build independence and reduce the cost of care for this population.

**Trial Registration:**

Australian New Zealand Clinical Trials Registry (ANZCTR) ACTRN12622000835741, https://www.anzctr.org.au/ACTRN12622000835741.aspx

**International Registered Report Identifier (IRRID):**

DERR1-10.2196/48503

## Introduction

### Overview

Acquired brain injury (ABI) refers to damage to the brain that occurs after birth and includes traumatic brain injury, stroke, infection, anoxia or hypoxia, and brain cancer to name the most common [1]. Cognitive impairments, including damage to higher-order executive functions, are frequently observed after ABI. Common executive function impairments include issues with prospective memory, flexibility, judgment, insight, planning and organization, and initiation of functional tasks [2]. Executive impairments can have a significant impact on functional outcomes and adversely affect participation in areas such as employment, leisure pursuits, relationships, and independent living [3-5].

### Assistive Technology for Executive Function Support

A growing range of electronic assistive technologies is available, which may compensate for a number of challenges to participation. For instance, smartphones and tablets used by the wider population are emerging as useful tools for developing independence and participation after ABI [6-9]. To date, most studies evaluating the efficacy of assistive technology in providing support to compensate for executive impairments have focused on prospective memory compared with other components of executive function. The strongest evidence to date has come from a small number of randomized controlled trials testing the efficacy of delivering reminders to reduce prospective memory failures through text messages or other auditory cues delivered by personal digital devices or mobile phones [10,11]. To date, few studies have investigated the efficacy of assistive technology in supporting other areas of executive function, such as supporting goal-directed behavior to undertake functional therapy [12,13] or enhancing executive monitoring of daily intentions [14].

As the assistive technology field has been rapidly evolving, there are growing platforms and means for delivering support for executive functions. For example, home hubs constitute a more specialized type of multifunctional device. One example of such devices is “Sofihub,” which provides home-based movement sensing, audio-prompting technology (similar in principle to “Alexa” or “Google Home”). Sofihub was designed and marketed for people with disabilities, including those with cognitive impairment [15]. Fernando et al [15] provided preliminary evidence of the effectiveness of Sofihub in augmenting human support for people with executive dysfunction, including impaired initiation. The system provided prerecorded verbal prompts to participants at set times or triggered by sensors detecting movement. The verbal prompts targeted self-care activities (eg, showering, teeth cleaning, and medication administration), household tasks (eg, cleaning and putting out garbage), and reminders to take necessary items (eg, phone, keys, and hearing aids) when leaving the house.

In Australia, the National Disability Insurance Agency has identified that assistive technology offers the potential to reduce the lifetime care costs of people with severe disabilities [16]. Nevertheless, to date, there is limited published evidence regarding the use of technology in the delivery of support to people with ABI in a range of community settings [17]. Specific to electronic personal assistive devices, there is insufficient evidence to recommend any practice standards [18]. This limits the capacity of people with ABI and their supporters, including family, carers, and health professionals, to effectively implement and harness emerging technologies within community living.

### Objectives

This paper outlines the study protocol for a series of single-case experimental designs (SCEDs) to evaluate the effectiveness of smart home, mobile, and/or wearable technologies for executive function support following ABI. The findings from the Sofihub trial [15] and other published evidence identify SCED as the principal methodology used to evaluate technological solutions for people with ABI [18]. The rigorous methodology of SCED enables it to test for cause-effect functional relationships between the intervention—in this case, smart home, mobile technology, or wearable technologies—and its effect in changing a behavior (eg, an increase in the number of steps in a specified task completed following a prompt from smart devices and a corresponding decrease in the number of verbal cues required from a support person) [19-21]. However, to date, many SCEDs have been of low scientific quality [22,23], and therefore, there is a need for more methodologically rigorous, evidence-based research to better understand the benefits of the introduction of technological aides [24]. The aim of this paper is to present a study protocol that will examine the efficacy of assistive technology (including home-based, mobile, and wearable technologies) in reducing executive function difficulties and care needs experienced by people with ABI.

## Methods

### Study Design

A series of SCEDs will be used to evaluate the effectiveness of the intervention technologies. The choice of design will be individualized for each participant based on the type of technology used in the intervention, the difficulty level of the behavior targeted for change, and the anticipated rate of change. It is expected that the most common design will be a withdrawal A_1_-B_1_-A_2_-B_2_ design (where A denotes the baseline phase and B denotes the intervention phase). However, multiple baseline, alternating treatments, changing criterion, and combination designs may also be used [25]. Decisions regarding the design to be implemented will be made on a case-by-case basis by the research team.

Each SCED will be planned using the Risk of Bias in N-of-1 Trials Scale [26,27] to maximize internal and external validity and will be conducted over approximately a 12-month period. The Risk of Bias in N-of-1 Trials Scale is a 15-item critical appraisal tool that evaluates the methodological quality of intervention studies using a single-case methodology. It comprises 2 subscales: internal validity and external validity and interpretation.

The report of each case will be prepared in accordance with the SCRIBE (Single-Case Reporting Guideline in Behavioral Interventions) statement [28] using a customized Microsoft Excel spreadsheet (Multimedia Appendix 1) to enable electronic record keeping. The SCRIBE is a 26-item reporting guideline developed in the CONSORT (Consolidated Standards of Reporting Trials) tradition to facilitate clear, complete, and transparent reporting of the study.

### Ethics Approval, Informed Consent, and Participation

The study design, recruitment, and data collection procedures were approved by the South Western Sydney Local Health District and Monash University Human Research Ethics Committees (Project IDs 2019/ETH14038 and 27923). The trial has been registered with the Australian New Zealand Clinical Trials Registry (ACTRN12622000835741). All participants will provide written informed consent before participating in the study. Each phase of the study will be monitored closely, and—as detailed in the procedures section—a customized Microsoft Excel spreadsheet (Multimedia Appendix 1) will be used to document and manage any adverse events or harms.

### Participant Eligibility

The inclusion criteria are as follows: participants will be aged ≥18 years, experience executive dysfunction following ABI, have substantial support needs for everyday living, reside in community dwellings, and have sufficient cognitive capacity to provide informed consent (determined by a review of any available neuropsychological assessment and/or in consultation with their treating allied health professionals). Participants will not be excluded based on their living location (metropolitan vs regional) or living situation (alone or with others). Exclusion criteria included people with current severe mental health problems or challenging behaviors.

Standardized clinical measures will be used to screen for eligibility. The instruments are described in Multimedia Appendix 2 [29-39]. The Frontal Systems Behavior Scale (FrSBe) [40] will be used to screen for executive dysfunction and the Care and Needs Scale [41] will be used for support needs. The Health of the Nation Outcome Scale—Acquired Brain Injury [42] will be used to identify severe mental health problems, and the Overt Behavior Scale–Adult [33] will be used for challenging behaviors.

### Setting

All data collection and assistive technology interventions of consenting participants will be carried out in the community, either their place of residence or work environment.

### Measures and Materials

#### Overview

All screening and outcome measures are described in Multimedia Appendix 2, along with two contextual measures: (1) Assessing Needs and Supports in Relation to Assistive Technology (A-AT; an unpublished semistructured interview) and (2) the World Health Organization Disability Assessment Schedule [34]. These will be administered to better understand participants’ functions, goals, and use of assistive technology. All published instruments have been used extensively in previous research in the field of ABI.

#### Primary Outcome Measure

##### Measures of Target Behavior(s)

In consultation with each individual participant, target behavior(s) will be identified based on their personal goal(s) for executive function support and/or participation in activities within home and community settings. The target behavior(s) will be tailored to each participant, and, as such, the measurement of the behavior will vary among participants. Target behaviors will be very specific, for example, frequency of occurrence or duration of a behavior, number of steps of an activity completed, or number of prompts from a support person. The frequency of measurement of the target behavior(s) will vary depending on the nature of the target behavior(s), but they will be measured, as appropriate, continuously throughout the baseline and intervention phases.

##### Goal Attainment Scaling

The Goal Attainment Scaling will be used to evaluate the level of goal attainment linked to the identified target behavior. Personalized evaluation scales ranging from +2 to −2 will be developed based on the framework of Krasny-Pacini et al [43] to ensure that the scales are a valid, reliable, and meaningful outcome measure.

#### Secondary Outcome Measures

The reason for including secondary measures is for the purpose of generalization and to determine whether the intervention has had effects on broader aspects of the participant’s functioning. The secondary outcome measures are as illustrated in the following sections.

##### Community Integration Questionnaire-Revised

The Community Integration Questionnaire-Revised [44] is an 18-item scale, which will be used to measure changes in community integration across four domains: (1) home integration (eg, meal preparation and housework), (2) social integration (eg, shopping, visiting friends, and leisure activities), (3) productive activity (eg, full-time vs part-time work, school, and volunteer activities), and (4) electronic social networking enabled social integration.

##### EuroQol-5 Dimensions Instrument

The self-complete (participant rated) and/or proxy (completed by a family member or paid support person(s) (ie, support worker, house manager, and allied health professional) versions of the EuroQol-5 Dimensions Instrument (EQ-5D-5L) [45] will provide a profile of health-related quality of life for the participant. The questionnaire has two components: (1) health state description and (2) evaluation. In the description section, they will be asked to rate 5 dimensions of health (mobility, self-care, usual activities, pain or discomfort, and anxiety or depression). In the evaluation part, they will be asked to indicate their overall health status (“TODAY”) using the visual analog scale from 0 to 100 with the end points labeled “the worst health you can imagine” to “the best health you can imagine,” respectively.

##### Psychosocial Impact of Assistive Devices Scale

The Psychosocial Impact of Assistive Devices Scale [46] will be used to measure the psychosocial effects the assistive technology device has had on the participant. It is a 26-item questionnaire, which will be used to measure the impact the assistive device has had on the participants’ sense of competence, adaptability, and self-esteem in daily life.

##### Quebec User Evaluation of Satisfaction With Technology

The Quebec User Evaluation of Satisfaction with Assistive Technology, version 2.0 [39], is a 12-item scale that will be used to measure the participants’ satisfaction with a technology device and its related services. This includes physical properties (eg, size, weight, ease of use, and effectiveness), and, if applicable, service delivery, maintenance, and follow-up services. The final part of the measure asks participants to choose the 3 assistive technology satisfaction items that are most important to them from a total of 12 items.

##### Disability Support Use and Cost

If agreed by the participant as part of the consent process, disability support costs will be sourced from an administration database of their funding organization to ascertain whether the assistive technology intervention impacted disability support use and cost. These data will be augmented with discussions with the participants (and/or their proxy) using a Participant Economic Evaluation Questionnaire (Multimedia Appendix 3) to ensure that all cost data, including informal supporter costs, have been accurately captured. Data will be gathered preintervention and after the second intervention. Where costs are not available for disability support through the funding organization, market rates will be applied, with the cost of informal care based on the Australian minimum wage [47]. All costs will be inflated to 2022-2023 by applying the Consumer Price Index [48].

### Blinding

Blinding in SCEDs refers to whether the participant, practitioner, and assessor are blind to the phase of the experiment. Blinding of participants will usually not be possible, given the nature of the intervention. However, the intervention is delivered by an assistive technology device, without the need for human involvement, thus eliminating human error and minimizing the risk of bias. Hence, for all intents and purposes, the “practitioner” (ie, the technology) can be considered blind to phase. Similarly, for each participant, the assessment data will be generated automatically from the assistive technology device, without the need for human involvement. Thus, the “assessor” (ie, the technology) can be considered blind to phase. In addition, data analysis will be performed by a statistician who will not be involved in discussions with the research group. The statistician will be blinded to all aspects of the intervention, including the specific phases in which data were collected.

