#### Phase 1: Baseline (A) Phase

Preintervention (secondary) measures will be administered (Multimedia Appendices 2 and 4). In addition, disability support costs will be sourced (Multimedia Appendix 3). During the baseline phase, the target behavior(s) will be measured repeatedly before implementing the intervention. Accordingly, this phase will serve as the control condition and include a minimum of 5 data points. For some technologies, it may be possible to use system-generated log reports to generate the target behavior data during the baseline (and intervention) phases. As such, the technology will be set up or installed (but during the baseline phase, it will not be activated, ie, for reminders or prompts) by either the occupational therapist to the research group or an external provider. If system-generated log reports are not possible, behavioral recordings of the target behavior(s) will be used.

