#### Phase 2: Intervention (B) Phase

The technology will be installed, worn, and/or activated by an occupational therapist in the research group or an external provider. If required, participants (and/or their proxy) will receive a single 1-hour orientation and training session by a member of the research group on how to use the technology. Any barriers to technology use will also be identified and ameliorated if possible. The target behavior will be measured continuously throughout the intervention phase, with a minimum of 5 data points.

Depending on the specific study design for each participant, there will be subsequent phases (for A-B-A-B withdrawal designs), subphases of the intervention (for changing criterion designs), staggered introduction of the intervention across multiple target behaviors (for multiple baseline designs), or alternating interventions in rapid succession (for alternating-treatment designs). Combination designs can also be used for this purpose.

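### The blinding section treats the assessor as blind for every participant because the device generates the data, but the procedures allow behavioral recordings and rated primary outcomes

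*Protocol article*

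**What the plan says.** The Blinding section accepts that participants can usually not be blinded, then argues that the other two roles are filled by the technology.

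- **Practitioner:** "the intervention is delivered by an assistive technology device, without the need for human involvement, thus eliminating human error and minimizing the risk of bias". The technology, as practitioner, is then treated as blind to phase.
- **Assessor:** "for each participant, the assessment data will be generated automatically from the assistive technology device, without the need for human involvement". The technology, as assessor, is treated as blind on the same ground.
- **Analyst:** a statistician who takes no part in the research group's discussions analyses the data without knowing the phases.

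The procedures and outcome sections read differently.

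- **Phase 1: Baseline (A) Phase:** "For some technologies, it may be possible to use system-generated log reports to generate the target behavior data". The next step is the alternative: "If system-generated log reports are not possible, behavioral recordings of the target behavior(s) will be used".
- **Measures of Target Behavior(s):** the examples include "number of prompts from a support person".
- **Goal Attainment Scaling:** placed under the Primary Outcome Measure heading, as a personalized scale from +2 to −2. The rater is not named.
- **Phase 2: Intervention (B) Phase:** people set the device going: "The technology will be installed, worn, and/or activated by an occupational therapist in the research group or an external provider". Where there is a need, the participant or proxy "will receive a single 1-hour orientation and training session by a member of the research group on how to use the technology". Barriers to use are also to be identified and, if possible, removed.

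**The concern.** In these single-case experiments the causal claim rests on comparing repeated measurements between baseline and intervention phases. If the person recording the behavior knows whether the device is active, expectation can move the record in the direction of an effect. The Blinding section tells the reader that this route is closed for every participant. The procedures leave it open for any participant whose behavior the device does not log.

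Support-person prompts are a clear example. The support person will normally know whether the device is prompting, and that person's own conduct is the outcome. A goal-attainment rating raises a similar question if the rater knows the phase.

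Blinding the statistician is worthwhile, but it protects the analysis only. It cannot remove bias that entered when the behavior was recorded or rated. A reader who takes the blinding statement at face value would give some cases more credit for bias control than their data collection earns.

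**Working it through.** The plan gives no figure on this point and no calculation applies. The check sets the statements side by side.

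| Issue | Blinding section | Procedures and outcomes |
|---|---|---|
| Source of assessment data | Automatic, for each participant | Logs possible for some technologies; behavioral recordings otherwise |
| Human part in assessment | None needed | Recordings; support-person prompts as an example; a rated goal scale |
| Human part in delivery | None needed | Staff or provider activate; training if required; barriers removed |

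**Step 1, source of the data.** A statement about each participant and a statement about some technologies can both hold only if every selected technology turns out to give usable logs in every phase. The baseline section does not assume this, since it plans for the opposite case. The two sections are therefore incompatible as plans.

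**Step 2, do recordings involve a person?** The baseline section does not say who or what makes them. Human involvement in recording or scoring is an inference from the contrast with system-generated logs. The article does not say that whoever records or scores is masked to phase. The blindness asserted for the assessor rests wholly on the data being automatic, so it does not carry over to the fallback.

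**Step 3, do the primary outcomes fit automatic capture?** Support-person prompts are one example in a list and are not assigned to any participant. Some devices might capture them. Goal Attainment Scaling is a rating. Where its levels are defined by a device-logged count, a level could be read off mechanically, but the article does not say that it will be. Neither outcome supports a claim of automatic data for all participants.

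**Step 4, delivery.** Once the device is running, prompts may well be issued without anyone present. Activation at the start of the intervention phase is done by a therapist or provider who knows the phase has begun. Training applies only if required; activation and barrier removal carry no such condition. The statement holds for the prompts and is too broad for the intervention as a whole.

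**Step 5, number affected.** Recruitment is up to 10 participants, and target behavior and device are chosen case by case. The article does not say how many will lack device logs, so the range is 0 to 10 of up to 10.

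**The case against.** **What stands on the other side.** The practitioner statement is hedged, and it can fairly be read as describing the delivery of prompts, with activation and training as surrounding steps. That limb is weaker than the assessor limb and calls for qualification rather than reversal. Per-participant outcome details are to be recorded on the SCRIBE checklist, and the appendix summarizing data collection procedures is not shown; either may name the recorder. Neither would remove the conflict, because the Blinding section speaks for each participant without exception.

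**Stronger readings the documents do not support.**

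- *A switch from human recording in baseline to device logging in intervention.* A reader might infer this because the intervention section allows technology to be installed or worn at that point. The baseline section points the other way: logs are meant to serve both phases, and for that reason the device is set up but left inactive in baseline. The fallback reads naturally as the source for the same phases. A switch is not ruled out in words, but it is not a stated plan, and any significance calculation built on it would measure assumptions from outside the protocol.
- *Primary outcomes known to be recorded by unblinded people.* With 0 of 10 in the possible range, this cannot be said as fact.
- *An inflated internal-validity rating.* Study Design uses the Risk of Bias in N-of-1 Trials Scale to plan each case. It reports no rating and relies on none.

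**Conclusion.** The assessor-blinding claim is wrong as written. It asserts for every participant a property that the baseline procedures make conditional on the technology, and it does not fit support-person prompts or goal-attainment ratings as primary outcomes. The practitioner claim is too broad but only partly contradicted.

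The size is open: 0 to 10 of up to 10 participants, with no basis in the article for a narrower range or for the direction and amount of any bias. The conclusion assumes that behavioral recordings involve a person at the recording or scoring stage, which the contrast with system logs implies but the text does not state. The conflict between an unconditional and a conditional statement about the data source stands without that assumption.

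**What to change.** **Blinding section.**

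- Limit the assessor claim to target behaviors logged by the device in all phases.
- State that behavioral recordings and Goal Attainment Scaling are not assessor-blind unless scored by someone masked to phase.
- Restrict the practitioner claim to automated delivery of prompts, and note that staff or a provider activate the device, train the participant if required and deal with barriers at the start of the intervention phase.

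**Baseline section.**

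- Add a sentence such as: *For a given participant and target behavior, the same measurement method is used in all phases; if device logs are not available in baseline, behavioral recordings are used in every phase.* This makes explicit what the section already suggests.
- Where recordings are stored, have existing team members score them in random order with phase labels removed. Do this only where the recording does not itself reveal the phase, for instance by capturing the device or its prompts. Otherwise report that case as not assessor-blind.

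**Cost.** Protocol wording, a note of the data source for each case, and slight extra scoring work. Some cases will carry a less favourable blinding statement. No treatment or schedule changes.

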## Results

Recruitment began in June 2022 but has been impacted by the unprecedented COVID-19 pandemic. The data collection is expected to be completed by March 2024. Only data from participants who complete all baseline and intervention phases of the study will be included in the analyses; however, reasons for withdrawal will be documented (eg, hospitalization due to deteriorating health).

Participant raw data from the publicly available contextual, secondary outcome, and screening measures will be entered into a Microsoft Excel spreadsheet (Multimedia Appendix 4). The spreadsheet contains formulas and calculations that automatically calculate scores and subscores (as per author guidelines for each measure). Test booklets will be used to enter and score the participant data from the FrSBe.

The target behavior data collected during the baseline and intervention phases will be entered or imported into SPSS statistical software (version 29; IBM Corp). Data for each participant will be evaluated separately using both structured visual analyses and statistical techniques suitable for within-subject, time-series data. Structured visual analysis will use the standard protocol of Kratochwill et al [52]. It will focus on important features of the data making both within- and between-phase comparisons for response level, trend, variability, immediacy, consistency, and overlap. The Tau-U technique [53] or another suitable technique (depending on the individual data patterns) will be used to statistically quantify the overlap and generate effect sizes. The results will offer new insights into the application of various electronic assistive technologies for executive function support following ABI.

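### Blinding the statistician to phase is largely nominal in baseline-first designs, because the planned analyses need time-ordered, phase-grouped data and the order gives the condition away

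*Protocol article*

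**What the plan says.** The Blinding section first defines blinding in a single-case experiment as not knowing the phase. It then says that "data analysis will be performed by a statistician who will not be involved in discussions with the research group", and that "The statistician will be blinded to all aspects of the intervention, including the specific phases in which data were collected".

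The Results section describes a structured visual analysis "making both within- and between-phase comparisons for response level, trend, variability, immediacy, consistency, and overlap". For the effect size it says: "The Tau-U technique [53] or another suitable technique (depending on the individual data patterns) will be used to statistically quantify the overlap".

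On phase order, the Study Design section says: "It is expected that the most common design will be a withdrawal A_1_-B_1_-A_2_-B_2_ design". It also allows several other designs, alternating treatments among them. The section on Phase 1 says that "the target behavior(s) will be measured repeatedly before implementing the intervention". The Phase 1 and Phase 2 sections each set a minimum of 5 data points.

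**The concern.** The same person is said not to know the phase and to carry out analyses built on phase. If the analyst can infer the condition, the protection against analyst bias is weaker than a case report repeating this statement would suggest.

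This matters because the analyst has discretion. Visual analysis relies on judgement, and the article lets the statistician move to "another suitable technique (depending on the individual data patterns"), so the technique may be chosen after the series has been seen. The other protections from blinding are also limited. Participants will usually not be blinded. The assessor counts as blind because the device generates the data, yet the Phase 1 section allows behavioural recordings where system logs are not possible. The statistician is the one human role for which phase blinding is claimed.

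**Working it through.** The article gives no figure to reproduce on this point, so the check is mainly one of logic, with a small illustration.

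**1. What each planned analysis needs**

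| Analysis | Points grouped by phase | Time order | Which phase is baseline |
|---|---|---|---|
| Level, variability | yes | no | no |
| Plain non-overlap Tau | yes | no | only for the sign |
| Trend | yes | yes | no |
| Immediacy | yes, with the change point | yes | no |
| Consistency | yes, and which phases are alike | no | no |
| Tau-U corrected for baseline trend | yes | yes | yes |

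**2. Illustration.** The values are assumed; only the 5 points per phase come from the article (its stated minimum).
- A1 = 2, 3, 2, 4, 3; B1 = 5, 6, 7, 6, 8
- A2 = 4, 3, 3, 2, 3; B2 = 6, 7, 8, 8, 9

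S(A,B) sums the sign of (b - a) over all 5 × 5 = 25 pairs. S(A) is the same sum over time-ordered pairs within the phase treated as baseline.
- Plain Tau = S(A,B) / 25
- Trend-corrected Tau-U = [S(A,B) - S(A)] / 25

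Every B value exceeds every A value, so S(A,B) = 25 in both pairs of phases. The within-phase sums are S(A1) = 4, S(B1) = 7, S(A2) = -5 and S(B2) = 9.

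| Pair | Statistic | True labels | Labels swapped |
|---|---|---|---|
| A1, B1 | Plain Tau | 25/25 = +1.00 | -25/25 = -1.00 |
| A1, B1 | Trend-corrected | (25 - 4)/25 = +0.84 | (-25 - 7)/25 = -1.28 |
| A2, B2 | Plain Tau | 25/25 = +1.00 | -25/25 = -1.00 |
| A2, B2 | Trend-corrected | (25 + 5)/25 = +1.20 | (-25 - 9)/25 = -1.36 |

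Plain Tau changes only in sign, so it can be computed under neutral codes and unmasked later. The trend-corrected form also changes in size, so it needs the baseline identified.

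**3. With no grouping at all.** The 10 points of A1 and B1, taken without order, can be split 5 against 5 in C(10,5) = 252 ways. Plain Tau over those splits runs from -1.0 to +1.0, so the data without phase grouping give no determinate answer.

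**4. With order but no boundaries.** If each of four consecutive phases has at least 5 points, a series of 20 points has only one possible set of boundaries. A series of 24 has C(7,3) = 35 and one of 40 has C(23,3) = 1,771. Beyond the minimum length, the analyst must therefore be given the boundaries.

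**5. With order and boundaries.** Baseline is the first phase. In an A-B-A-B series, block 1 is A, block 2 is B, and so on. Renaming the blocks X and Y conceals nothing from an analyst who knows the design. The same holds for the start of any other design that opens with a baseline.

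**The case against.** The strongest defence is that the sentence means masking of condition, not of grouping. Neutral codes would then allow level, variability and plain Tau to be computed blind, and the article does not commit to the trend-corrected Tau-U. The coding procedure could sit in the full protocol, which a condensed article need not repeat. For a fixed contrast, moreover, Tau-U is arithmetic and does not depend on what the analyst knows. The article also does not say outright who performs the visual analysis.

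Much of this stands, and it limits the point. A reader might infer that the planned analysis cannot be run, that no safeguard exists, or that every participant and every primary analysis is affected. The documents support none of these:
- Several planned statistics need grouping only.
- Separation from the research group's discussions and masking to the technology are untouched by the argument.
- The design is individualised, A-B-A-B is only the expected commonest one, and coded conditions could stay masked under alternating treatments.
- Goal Attainment Scaling, also listed under the primary outcome, does not depend on Tau-U.

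The defence does not rescue the sentence for baseline-first designs. Trend and immediacy need ordered data, and order reveals the phase whatever codes are used, so no unseen coding procedure restores the stated property while those analyses are kept. Fixed arithmetic also does not remove bias from visual judgement or from a technique chosen after seeing the series.

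**Conclusion.** Wrong as written. The article makes a general claim of phase blinding for the analyst that its own analyses cannot honour in baseline-first designs, including the one expected to be commonest. There the masking is largely nominal. How many of the up to 10 cases this covers cannot be stated, because design is chosen case by case.

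The conclusion assumes that the statistician knows the type of design and receives the series in time order with phase boundaries, as trend and immediacy require. It also takes the Blinding section at its word that the statistician performs the data analysis. The figures above show which statistics depend on knowing the baseline; they do not estimate any bias in this trial.

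**What to change.** In the Blinding section, describe the statistician as independent of the research group and masked to the technology and to participant identity. Claim phase masking only for designs in which coded conditions can be concealed, such as alternating treatments.

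In the Results section, replace the choice of technique by data pattern with a specification fixed for each case before outcome data reach the statistician. It should state the contrasts, the direction of improvement, the rule for trend correction and the effect-size technique. Direction needs stating because the targets named as examples, such as steps completed and prompts from a support person, would improve in opposite directions.

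The cost is giving up the general phase-blinding claim and a little preparation per case. Randomised phase-change points would alter the experimental design and are not needed for this correction.
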